**Enrollment**						
Eligibility screen	X					
Informed consent	X					
Randomization		X				
**Intervention**						
Embolization				X		
**Assessments**						
Demographics, medical history, laboratory data			X			
Neurological tests			X		X	X
Computed tomography			X		X	X
Complications				X	X	X

### Sample size {14}

Because of the potential of notable morbidity, recurrent cSDH is considered both a clinically relevant and methodologically reliable, objective primary trial endpoint.

In one of the largest studies to date, Ban et al. compared a prospective series of 72 patients with cSDH undergoing MMA embolization with a historic standard-of-care group of 469 subjects. The overall risk difference (irrespective of hematoma evacuation) was estimated at 26% (95% CI 21 to 31%) in favor of endovascular management. There is much variability in reported cSDH recurrence risks with either treatment option, and unclarity about the realistic benefit of combined surgical and interventional therapy.

In view of the results of published studies (in particular Ban et al.), we conservatively presume recurrence rates of 30% in the control and 10% in the experimental arm during an observation period of 3 months.

Since our assumptions are subject to uncertainty, we will employ an adaptive design according to O’Brien-Fleming with one planned interim analysis to decide about the further trial progress, and to modify the target sample size if necessary and/or reasonable. For a power of 80% and a total alpha of 5%, data from 138 patients (i.e., 69 per group) are needed to detect a risk difference of 20% by a *z*-test for independent samples. Assuming a drop-out and lost-to-follow-up rate of 10%, we plan to enroll 154 patients (i.e., 77 per treatment arm) unless the interim look prompts any adjustment.

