## Statistical methods

### Statistical methods for primary and secondary outcomes {20a}

The primary outcome, i.e., reduction in cSDH recurrence through the experimental, surgical plus endovascular treatment, compared to surgery alone, will be analyzed using a chi-square fourfold test for independent samples. The two-sided significance level *α* is set at 5% and the power at 80%. Superiority of the experimental intervention over control is assumed, if the resulting *p*-value is below the nominal significance level of 0.00031 at the time of interim analysis (prompting early trial termination), or the nominal significance level of 0.0469 at the time of final analysis.

Secondary categorical outcomes will be investigated by the Cochran-Mantel-Haenszel (CMH), chi-square, or Fisher’s exact test (if one of the cell frequencies is <5). Recurrence-associated complications, complications associated with endovascular embolization, and (serious) adverse events will be expressed as absolute and relative frequencies.

Exploratory analyses will be performed for the distribution of genetic variants and their correlation (by Pearson’s *phi*-coefficient) with factor XIII deficiency (<70%) across the entire cohort without stratification for the type of intervention. The closer the *phi*-coefficient to 1 or -1, the stronger the association (or predisposition) between genetic variants and factor XIII deficiency. Advanced analyses will be performed to study the association between heterozygous, homozygous, and wild type variants, factor XIII activity, and cSDH recurrence.

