### Interim analyses {21b}

The planned interim analysis according to the O’Brien-Fleming design will be conducted after the recruitment of half of the target sample. Given the predicted recruitment speed and rate will be reached on time, the interim analysis will be conducted 12 months after first-patient-in (plus 3 months of follow-up), corresponding to 77 included patients and 69 evaluable data sets. If a statistically significant advantage in the recurrence rate of the experimental group can be demonstrated at the time of the interim analysis with a *p*-value of the chi-squared test of <0.0031, the experimental therapy will be assumed to be superior to the standard of care, leading to premature termination of the study. If the effect size is lower than presumed, a larger sample size and enrolment of additional trial sites must be considered. Investigators will discuss this option together with the funding body and the DSMB. If the likely risk difference between treatments is much smaller than expected and the recalculated sample size exceeds numbers which cannot be achieved, the trial will be terminated for futility. The trial will also be terminated early if the surgery-only control group turns out to be superior to combined management in any case, or if major novel scientific evidence shows any substantial favor of one over the other approach.

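### The stated 138 evaluable patients do not follow from the named z-test at 80% power, which needs 124 to 126; the discrepancy is conservative and its origin is not stated

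*Protocol article*

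**What the plan says.** All references are to the protocol article.

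- **Sample size {14}**, rates: "we conservatively presume recurrence rates of 30% in the control and 10% in the experimental arm".
- **Sample size {14}**, result: "For a power of 80% and a total alpha of 5%, data from 138 patients (i.e., 69 per group) are needed". The sentence names a z-test for independent samples as the method.
- **Sample size {14}**, enrolment: after a 10% allowance for drop-out and loss to follow-up, "we plan to enroll 154 patients (i.e., 77 per treatment arm) unless the interim look prompts any adjustment".
- **Statistical methods for primary and secondary outcomes {20a}**: the primary outcome "will be analyzed using a chi-square fourfold test for independent samples". The 5% level is two-sided, and the nominal level at the final analysis is 0.0469.
- **Interim analyses {21b}**: the look takes place at half the target, "corresponding to 77 included patients and 69 evaluable data sets". The sample size may be changed afterwards. The trial may stop for futility if the likely difference is much smaller than planned and the recalculated size is out of reach.

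**The concern.** The paragraph fixes everything a reader needs to recompute the number: both rates, sidedness, alpha, power, allocation and test. The analysis test matches, because the uncorrected chi-square test on a fourfold table is the square of the pooled z-test. Yet the recomputed size is about 10% below the stated one.

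A conservative sample size does no direct harm to the trial's conclusion. Three things still depend on the figure:

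1. The power claimed for the trial is not the power of the test it names.
2. The interim timing, 69 evaluable data sets, is half of 138.
3. The interim section allows the size to be changed if the effect is smaller than assumed. A recalculation with the named formula would differ from the plan by about 10% before any data effect, and a reader could not tell a change in method from a change in the effect estimate.

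**Working it through.** **Inputs.** Rates p1 = 0.30 and p2 = 0.10, so the difference is 0.20 and the mean rate is 0.20; power 80%, total alpha 5%, z-test, 10% drop-out (Sample size {14}). Two-sided testing, final level 0.0469 (Statistical methods {20a}). Allocation 1:1 (Trial design {8}).

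**Step 1. The enrolment step reproduces.** 138 / 0.9 = 153.3, rounded up to 154; per arm 69 / 0.9 = 76.7, rounded up to 77.

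**Step 2. The evaluable number does not.** For the pooled z-test, with z the normal quantiles for alpha and power,

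n per group = [z_alpha × √(2 × 0.20 × 0.80) + z_power × √(0.30 × 0.70 + 0.10 × 0.90)]² / 0.20²

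- Alpha 0.05: [1.960 × √0.32 + 0.842 × √0.30]² / 0.04 = (1.1087 + 0.4610)² / 0.04 = 61.6, so 62 per group, **124** in total.
- Alpha 0.0469: [1.987 × √0.32 + 0.842 × √0.30]² / 0.04 = (1.1241 + 0.4610)² / 0.04 = 62.8, so 63 per group, **126** in total.

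**Step 3. Variants of the named method.**

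| Variant | Per group |
|---|---|
| Unpooled variance, 0.05 | 59 |
| Arcsine, 0.05 | 60 |
| One-sided 5% | 49 |
| Continuity-corrected, 0.05 | 72 |
| Classic O'Brien-Fleming, inflation 1.008 | 63 (62.1 rounded up) |
| Lan-DeMets O'Brien-Fleming, inflation 1.004 | 62 (61.8 rounded up) |
| The protocol's own boundaries, inflation 1.017 to 1.019 | 63 |

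The protocol prints the interim level as 0.00031 in one place and 0.0031 in another. Both were tried, and the answer is the same. No variant gives 69.

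**Step 4. Power at 69 per group.** Power = Φ[(0.20 × √69 − z_alpha × √0.32) / √0.30].

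- Alpha 0.05: (1.6613 − 1.1087) / 0.5477 = 1.009, so 84.3%.
- Alpha 0.0469: (1.6613 − 1.1241) / 0.5477 = 0.981, so 83.7%.
- Exact binomial power of the chi-square test: 85.7% at 0.05 and 85.5% at 0.0469. Simulation with the efficacy look also gives about 85.5%.

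**Step 5. Routes that do give 69 per group.**

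- Drop-out counted twice: 124 / 0.9 = 137.8, rounded up to 138; then 138 / 0.9, rounded up to 154. Per arm: 62 to 69 to 77.
- Fisher's exact test at a full 5%: power 79.97% at 68 per group and 80.7% at 69. At 0.0469 it is 79.4% at 69.
- A Pocock two-look inflation of 1.110: 61.6 × 1.110 = 68.4, rounded up to 69.

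The first does not match the text, which applies drop-out once. The second is not the test named for the primary outcome. The third is not the declared boundary.

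**The case against.** **Double counting.** A reader might infer from 124 to 138 to 154 that drop-out was certainly applied twice. The document does not support that. It applies the 10% once, and the interim section treats 138 as evaluable, since 69 evaluable of 77 included is half of 138 and half of 154. The arithmetic fits at both steps, but two other routes also give 69 per group. It is a possibility to check and not a finding.

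**Underpowered or invalid.** A reader might also infer that the trial lacks power. It does not. The discrepancy runs in the safe direction under the protocol's assumptions, and even Fisher's exact test has about 80% power at 69 per group.

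**Futility.** The best objection to a replacement figure of 84% is that it counts the efficacy look only. The interim section also provides for a futility stop, and following one costs power. It gives no threshold, so any figure rests on an assumption. With Lan-DeMets O'Brien-Fleming efficacy bounds and one half-way look, 80% power needs 62.3 per group if the trial stops at an interim z below 0, 64.5 below 0.5, 68.1 below 0.8, and 72.2 below 1.0. At half-way, z = 0.8 is an observed difference of about 0.8 × √(0.32 / 34.5) = 0.077, or 8 points. By simulation of the chi-square test with 69 per group, power falls from about 85.5% to about 82% at a cut of 0.8 and to just under 80% at a cut of 1.0. This point stands: 84% may be stated only as ignoring futility. It does not rescue the sentence in the plan, because no futility allowance is mentioned there.

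**Consequence at the interim.** The protocol gives no recalculation formula and does not say that 138 is the reference. The risk of confusion at that point is plausible but not certain.

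**Conclusion.** The stated size is wrong for the method named. By the z-test at the stated rates, alpha and power, 124 to 126 evaluable patients are needed, not 138. The stated figure is 12 to 14 patients too high, about 10 to 11% (138 / 126 = 1.095; 138 / 124 = 1.113). With one 10% allowance, enrolment would be 138 to 140 (124 / 0.9 and 126 / 0.9), against 154 planned, a difference of 14 to 16. Power at 69 per group is about 84% by formula, or about 85.5% by exact calculation with the efficacy look.

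These figures assume 30% versus 10%, exactly 69 evaluable patients per group, and no futility stopping. An aggressive futility cut could bring the power back to about 80%. The error is conservative, it does not threaten the validity of the primary test, and where 138 came from is not established. It should be corrected because a stated basis of the trial cannot be reproduced and because the interim analysis builds on it.

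**What to change.** Keep 154 enrolled. Then do one of the following in the sample-size section:

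- **Restate the power.** Suggested wording: *138 evaluable patients give about 84% power for 30% versus 10% by the z/chi-square test under the two-look O'Brien-Fleming efficacy design, ignoring futility stopping; about 126 would give 80%.*
- **Or name what produced 138**: the test, the software and any sequential or futility inflation. If that was Fisher's exact test or a Pocock boundary, reconcile it with the chi-square analysis and the O'Brien-Fleming design stated elsewhere.

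In either case, confirm from the original calculation whether 138 already contains the drop-out allowance, and state the formula that any interim recalculation will use, so that it matches the one behind the planned size.

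Cost: a look at the original calculation and a rewording of one paragraph. No added patients, and no change to the test or the alpha.

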### Recruitment {15}

During a kick-off meeting, clinical investigators and trial supporting personnel will be trained in communicating with potential study participants and their relatives, documentation including screening logs, and other standard operating procedures established for trial purposes.

In agreement with the funding body, recruitment efficiency will be evaluated 9, 15, and 21 months after randomization of the first patient, using the observed to expected ratio and curve.

In case of insufficient enrollment (i.e., <25% of the number of patients included at a certain time point), investigators will take extra measures to improve recruitment (e.g., increasing awareness among all clinicians, nurses, therapists, expansion of the recruiting team, modification of eligibility criteria, etc.). While it is currently not intended to roll out this trial to other centers, we will negotiate with the funding body to include other institutions if trial aims cannot be achieved otherwise.

## Assignment of interventions: allocation

### Sequence generation {16a}

Patients will randomly be assigned to trial arms using a web platform and an extended stratified block algorithm. The algorithm guarantees even distribution of key baseline characteristics across the intervention and the control group.

### Concealment mechanism {16b}

Participants are randomized using secuTrial® (interActive Systems GmbH, Berlin, Germany), a web-based, GCP-compliant electronic data capture (EDC) system for collecting patient data in clinical trial, observational studies, and registries. It maintains allocation concealment as it does not release the randomization code until screening has been completed and the patient was cleared to be recruited onto the trial.

### Implementation {16c}

Extended stratified block algorithms generate an unpredictable allocation sequence. Random assignment by secuTrial® cannot be influenced by clinical investigators.

## Assignment of interventions: blinding

### Who will be blinded {17a}

Due to the surgical and interventional nature of trial modalities, blinding of both the immediately performing clinical investigators (i.e., neurosurgeons and interventional radiologists) and patients is almost impossible. While a sham procedure (i.e., placement of a transfemoral catheter and even infusion of a saline placebo) in the control group may be implemented, this is considered unethical as it exposes patients to additional harm without any possible benefit, given the primary endpoint.

Radiological experts evaluating baseline and follow-up CT scans after 1 and 3 months will be blinded to the randomly assigned treatment, assuring this is an observer-blinded trial.

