### Outcomes {12}

#### Primary outcome

The primary outcome is cSDH recurrence up to 3 months after surgery. Recurrence is defined by one and/or both of the following criteria:Recurrent cSDH with at least the same volume (±10%) compared to baseline findingsRecurrent cSDH which requires surgery

Recurrence of cSDH is operationalized as a binary outcome (i.e., recurrence or no recurrence) during a follow-up period of 3 months.

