## Data collection and management

### Plans for assessment and collection of outcomes {18a}

Data will be entered by clinical investigators and supporting trial personnel on electronic case report forms (eCRFs) created by secuTrial®.

Neurological examination comprises the modified Rankin scale for neurologic disability [36], the muscle function according to Janda [37], the presence of word finding disorders, hemiparesis, and anisocoria, as well as vigilance. Standard laboratory parameters will be taken from peripheral blood at baseline and during follow-up. The size and extent of cSDH will be measured on non-contrast CT scans.

The following parameters of recurrence-associated or intervention-associated complications will be documented for study purposes:

Recurrence-associated:Cerebral edemaCerebral infarction

Intervention-associated:Dissection of vessels by the guide wireDislocation of particles or coilsIschemia caused by internal-external vascular connectionsRetinal blindnessEpidural hematoma after MMA perforationInflammation or abscess at the puncture siteVascular fistula at the puncture siteVascular bulging at the puncture siteAllergic reaction to the contrast agentAcute renal failure

Complications not covered by predefined categories may be entered as free text in the eCRF.

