## Discussion

We herein describe the rationale, design, interventions, and methodological framework of a single-center, investigator-initiated, partially blinded, randomized controlled trial to test whether additional endovascular embolization of the MMA is superior to neurosurgical hematoma evacuation only in reducing the rate of recurrence in cSDH.

Current observational evidence suggests that postoperative occlusion of MMA branches may reduce the incidence of recurrent cSDH without major complications. Yet, a randomized controlled trial is urgently needed to evaluate the benefit-to-risk ratio of additional embolization of the MMA compared to the neurosurgical standard of care.

If combined surgical and interventional care turns out to be superior to surgery alone in this trial, this may prompt further confirmatory trials and, at best, may change clinical practice and guideline recommendations.

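### Blinded CT reading protects only the volume criterion of the primary endpoint; the re-operation criterion is not covered by the observer-blinded claim

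*Protocol article*

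**What the plan says.** Under Who will be blinded {17a}, the protocol article states that "blinding of both the immediately performing clinical investigators (i.e., neurosurgeons and interventional radiologists) and patients is almost impossible". The same section goes on to name the blinded assessors: "Radiological experts evaluating baseline and follow-up CT scans after 1 and 3 months". Their blinding is the only ground given for the claim that they "will be blinded to the randomly assigned treatment, assuring this is an observer-blinded trial".

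Under Primary outcome, the article says: "Recurrence is defined by one and/or both of the following criteria". The first criterion is a recurrent hematoma with at least the baseline volume, within 10%. The second is a recurrent hematoma that needs surgery. Either alone makes the patient an event.

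Sample size {14} adds that "recurrent cSDH is considered both a clinically relevant and methodologically reliable, objective primary trial endpoint". The Discussion is more cautious and describes a "single-center, investigator-initiated, partially blinded, randomized controlled trial". Plans for assessment and collection of outcomes {18a} says: "Data will be entered by clinical investigators and supporting trial personnel".

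**The concern.** Blinding the CT readers makes the volume criterion on the scheduled scans a masked assessment. It does nothing for the second criterion, where the event depends on a judgement that surgery is needed. The claims of observer blinding and of an objective endpoint are made for the endpoint as a whole, and they do not hold for that part.

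The primary risk difference is at stake. If knowledge of the arm shifts the threshold for re-operation, the recurrence rates can differ between arms without any difference in recurrence. More readiness to re-operate on controls, or restraint after embolization, would favour the intervention. More vigilance after a new procedure would work against it.

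**Working it through.** **Text comparison.** The claim rests on no figure in the plan, so nothing has to be reproduced first. The relevant statements, side by side:

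| Question | Volume criterion | Re-operation criterion |
|---|---|---|
| Sufficient alone for a primary event? | Yes | Yes |
| Threshold stated? | Baseline volume, ±10% | None |
| Blinded assessor named? | Yes, on baseline, 1-month and 3-month CT | None |
| Who judges? | Blinded radiologists | Not stated; presumably clinicians who know the arm |

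The last cell is an inference. The blinding section says that neurosurgeons can hardly be blinded, and no masked decision-maker or adjudicator is named.

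**Timing.** Follow-up CTs are scheduled at 1 and 3 months (±1 week; Participant timeline {13} and Table 1). A patient re-operated between visits becomes an event through the second criterion. The scan that prompted the operation is not among those the article assigns to blinded readers, and after evacuation the next scheduled CT need not show the recurrence.

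**Illustration of size.** Inputs from the article: 69 evaluable patients per arm and a 30% control recurrence rate (Sample size {14}); chi-square test at a nominal two-sided 0.0469 at the final analysis (Statistical methods {20a}). Assumptions not in the article: no true effect; underlying recurrence rate p of 30%, 20% or 15% in both arms; and d extra percentage points of re-operations counted in controls only. The interim look is ignored.

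Let X be events among controls, binomial(69, p + d), and Y events among embolized patients, binomial(69, p). With pooled rate q = (X + Y)/138, the test statistic is

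Z = [(X − Y)/69] / √[q(1 − q) × 2/69].

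The false-positive rate in favour of embolization is the sum of the exact probabilities of all pairs (X, Y) with X > Y and Z above the normal quantile at 1 − 0.0469/2.

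| Underlying rate p | d = 0 | d = 1 point | d = 3 points | d = 5 points |
|---|---|---|---|---|
| 30% (protocol's control rate) | 2.4% | 3.2% | 5.5% | 8.7% |
| 20% | 2.4% | 3.4% | 6.1% | 10.0% |
| 15% | 2.4% | 3.5% | 6.7% | 11.6% |

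In patients, 3 points is 0.03 × 69 ≈ 2.1 and 5 points is 0.05 × 69 ≈ 3.5. A shift of two to four patients in one arm is therefore enough to at least double the error rate. With equal arms the test is symmetric, so the same shift in the embolized arm would give the same rates of a false finding against embolization.

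**A second bias model.** Keep p = 30% in controls. Suppose a share s of events counts only through re-operation, and that re-operation is relatively less frequent by r in the embolized arm. The embolized rate is then 0.30 × (1 − s × r). For s = 50%, r = 10% it is 28.5%, and the false-positive rate is 3.7%. For s = 100%, r = 30% it is 21%, and the rate is 21.9%. The result depends heavily on s and r, and the article gives neither.

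**The case against.** The strongest reply is that the article is open about the limitation. It says that clinicians and patients are unblinded, explains why a sham procedure was rejected, and calls the trial partially blinded in the Discussion. The second criterion is also not pure discretion: a recurrent hematoma must be present, and some re-operated patients would meet the volume criterion anyway. Adjudication rules, handling of unscheduled scans and sensitivity analyses are commonly left to the full protocol or SAP, which are not shown. All of this stands, and it narrows the point to what the article asserts: blinded CT reading is given as what makes the trial observer-blinded, and the endpoint is called objective without qualification. Neither assertion covers the re-operation criterion.

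Three stronger readings are tempting and are not supported:

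- A reader might infer that the article says unblinded neurosurgeons decide on re-operation. It does not say who decides.
- A reader might infer that unscheduled scans are never read blind. The article lists scans that are read blind but does not exclude others; section {18a} speaks of CT measurement without limiting it to scheduled visits.
- A reader might infer that no planned analysis would reveal a bias. That cannot be known without the full protocol and SAP.

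Nor does one criterion of two mean half of the events; the article gives no split. Finally, the shifts of 1 to 5 points are assumptions. They show what a bias of that size would do, not that it is to be expected.

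**Conclusion.** The point holds in limited form. As written, the observer-blinded and objective descriptions are true of the CT volume criterion on scheduled scans and overstated for the re-operation criterion, which can create a primary event alone. At the protocol's own 30% rate, an assumed excess of 3 or 5 points of re-operations in controls would move the one-sided false-positive rate from 2.4% to 5.5% or 8.7%; at the lower rates of 20% and 15% the increase is somewhat larger. A 1-point excess matters little (3.2% to 3.5%). These figures rest on no true effect, 69 per arm, the final look alone and a bias in one direction. The real size and direction are unknown, which is a reason to measure the component separately. This should be corrected, but it does not invalidate the design.

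**What to change.** 1. Have the existing blinded readers read the CT preceding each re-operation, masked to arm and to the later decision, and record whether a recurrent collection is present and whether the volume criterion is met.
2. Report the volume and re-operation components separately by arm, next to the combined primary endpoint.
3. Add one sensitivity analysis that counts a re-operation as recurrence only if the blinded read confirms a recurrent collection.
4. Limit the observer-blinded and objective wording to the CT volume component, in line with the Discussion's description of a partially blinded trial. If the full protocol already provides masked adjudication, one sentence saying so would do in place of step 1.

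The cost is small. The number of extra readings is about the number of re-operations at most. Under the planning rates, expected recurrences are 69 × 0.30 + 69 × 0.10 = 20.7 + 6.9 ≈ 28 in total, of which re-operations are an unknown share. The readers are already in the trial, and one analysis is added. The primary endpoint, the sample size and the decision to operate stay as they are.
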